Conflicts of Interest: KR is a non-financial board member on the board of directors for RIBU Plasma Pty. Ltd. (Australia) and an inventor on patent WO/2024/013069 (Buske, C., & [name] (2024). Process, apparatus and use of an apparatus for producing a plasma-activated liquid. Patent No. WO2024013069. World Intellectual Property Organization). KR will not analyse or interpret the data.

## Introduction

Of the >1.2 million Australians living with diabetes, about 25% have a lifetime risk of developing a foot wound, >50% of those will develop infection, and >25% of those infections will become chronic/relapsing infections. Patients with diabetes-related foot disease often present initially without clinically-relevant infection; however, even with gold-standard podiatric care and wound dressing solutions, many of these patients will develop diabetes-related foot infection that require hospitalisation. Infections that progress to necrosis and osteomyelitis often require surgical management leading to wound debridement or amputations with severe consequences to patient quality-of-life, morbidity, and mortality; and significant healthcare costs. Mortality after diabetes-related amputation is notoriously high with 70% at 5 years for all patients with diabetes and 74% at 2 years for those undergoing dialysis.

Pathogens typically reside in biofilms, which are clusters of microbes embedded in a protective slime. Biofilms hamper the efficacy of antimicrobial therapies by impeding drugs to reach pathogens and allowing bacteria to establish resistance. The failure of best medical care with antibiotics, the lack of innovative products that are effective against biofilms, and the slow translation of promising treatments to human trials emphasise the urgent need to revolutionise infection control. We must find better treatments for multi-drug resistant (MDR) pathogens and biofilms while accelerating the translation of innovative therapies from bench to bedside. This is crucial if we want to lower morbidity and mortality linked to MDR infections, improve patients' quality-of-life, and reduce healthcare costs.

For this study, participants will have full wound standard-of-care provided by an experienced clinical trial wound nurse, with a wound rinse performed with one of two agents: saline control, or plasma-activated water (PAW). As described in the Investigator Brochure and below, this novel solution has the potential to be a rapid-acting wound cleaning agent that will kill bacteria in biofilm without engendering antibiotic-resistant organisms. As a first-in-human study of a product with a favourable safety profile, we expect this trial to place CALHN researchers and patients at the forefront of new infection control technologies.

## Investigational Product Rationale

Cold plasma is an ionized gas consisting of excited ions, free electrons and radicals. When cold plasma is discharged in water it enriches the liquid with reactive oxygen and nitrogen species (RONS), which increases the redox potential and decreases the pH. This creates an environment capable of effectively killing pathogens in vitro, while human cells remain unharmed due to internal mechanisms to neutralise RONS and pH. This makes cold plasma a potential breakthrough technology to improve infection control during wound management.

Plasma-activated water is safe to use and effective against MDR pathogens and biofilms in vitro. In collaboration with the company Plasmatrete, CI [name] and CI [name] evaluated 5 types of PAW for antibacterial and antibiofilm activity against a range of MDR pathogens, including methicillin-resistant *Staphylococcus aureus* (MRSA) as one of the most difficult-to-treat superbugs that is highlighted on the WHO's global priority list to guide discovery, research and development of new treatments for MDR infections. CI [name] and CI [name] identified one specific PAW type to show highest in vitro activity against MRSA planktonic

bacteria and biofilms, while being non-toxic to human skin cells (keratinocytes). Specifically, PAW exhibited >99.99% biofilm killing in microtiter assays, and reduced MRSA infection and accelerated skin wound healing in infected wounds in mice. Currently, CI’s [name] and [name] are investigating PAW in treating infected excisional wounds in pigs that most closely resemble human skin healing to better translate PAW as an antimicrobial topical treatment for wounds..

To our knowledge, this is the first application of plasma-activated water in human wound care. There is one registered study for plasma-activated saline wound treatment (NCT05924867) by First Affiliated Hospital Xi'an Jiaotong University, but this study has not been updated since June 2023 and is yet to enrol participants as of June 2025.

**Risk/Benefit Assessment**

As a first-in-human trial, some unforeseen risks to participants are unavoidable; however, all existing preclinical data highlights minimal risk to human cells and wound healing. As a topical application, it is highly unlikely that any application of PAW can have systemic effects. No participant will have PAW applied until completion of an ongoing large-animal (pig) preclinical study demonstrates no ill effects.

As a novel agent applied to open wounds, it is possible that localised skin irritation may occur; the trial and care team will be aware of this as the most likely adverse reaction and tailor a care plan for cases where it eventuates in order to limit impact of irritation on the wound microenvironment and healing.

Preclinical mouse and pig models showed no signs of pain or discomfort on application of PAW, and our patients with DFU, who are predominantly neuropathic, have a decreased capacity to feel localised foot pain. If patients with incomplete loss of sensation do report any pain or discomfort from the rinse application, saline will immediately be applied to wash away PAW and the event reported as an adverse reaction.

As a Phase I study in patients without severe infection, benefits to participants are expected to be muted. We expect participants randomised to the experimental arm of this study to have reduced bacterial load and recurrent infection during study; preclinical data suggests that wound healing may also be improved for this group. Regardless, we expect participants in both groups to benefit from improved personalised care experienced by typical clinical trial participants.

**2 STUDY OBJECTIVES AND OUTCOME MEASURES**

**Table 1 Study Objectives and Endpoints**

| Primary Objectives                                                                        | Primary Outcome Measures                                                                                                                                                                                                                                              |
|-------------------------------------------------------------------------------------------|-----------------------------------------------------------------------------------------------------------------------------------------------------------------------------------------------------------------------------------------------------------------------|
| To assess the safety and tolerability of PAW up to 6 weeks after initiation of treatment. | The primary safety analysis will be performed based on data collected up to 6 weeks after initiation of treatment. Assessment of safety will be based on the Incidence and severity of adverse reactions, including but not limited to skin irritation or maceration. |

| Secondary Objectives                                                              | Secondary Outcome Measures                                                                                                                                                                                                                                                                                                                                                                                                                                                         |
|-----------------------------------------------------------------------------------|------------------------------------------------------------------------------------------------------------------------------------------------------------------------------------------------------------------------------------------------------------------------------------------------------------------------------------------------------------------------------------------------------------------------------------------------------------------------------------|
| To evaluate the efficacy of PAW, at 12 and 18 weeks after initiation of treatment | 
Efficacy analysis will be performed based on data collected up to 18 weeks after initiation of treatment. Assessment of efficacy will be based on the following outcome measures of the study ulcer:
 
 
• Days to complete ulcer healing
 
• Presence and severity of infection
 
• Changes in wound quality based on ulcer assessment
 
• Quality of Life (Cardiff Wound Impact Schedule)
 
 |

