### **Overview of Study Visits**

Study procedures should be performed at relevant study visits in accordance with the schedule of procedures outlined in Table 1. The Principal Investigator or other study doctor will be present for study treatment at screening and at the week two visit at minimum to ensure patient safety and observe for AEs.

Participants will only be enrolled and randomised to study treatment if they meet all eligibility criteria, and none of the exclusion criteria.

Study visits will be arranged at Royal Adelaide Hospital and/or The Queen Elizabeth Hospital, aligning with patient clinical visit scheduling where possible to minimise inconvenience to participants. A window of plus or minus three days is permitted for Visits 1 to 6, and a window of plus or minus seven days is permitted for follow-up Visits 7-10. Study visits via home visit are permitted for Visits 3-10.

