### **Data collection**

Demographic data will include:

- Age
- Gender
- Ethnicity
- Race
- If the participant holds a healthcare card

Medical history will include (to the extent that details are known):

- Date of diabetes diagnosis
- Diabetes type

- History of peripheral artery disease and related conditions
- Details of peripheral neuropathy
- Date of ulcer onset
- Details of previous ulcer assessments
- Details of previous interventions/treatments relevant to DFU
- History of cardiovascular events
- History of renal disease with or without dialysis
- Use of immunosuppression
- Smoking status current / past

| Study period        | Screening | Treatment and Evaluation |                  |                  |                  |                  |                  |                                 |                  |                  |                     |
|---------------------|-----------|--------------------------|------------------|------------------|------------------|------------------|------------------|---------------------------------|------------------|------------------|---------------------|
| Visit number        |           | 1                        | 2                | 3                | 4                | 5                | 6                | 7                               | 8                | 9                | 10                  |
| Study Week          |           | 1
(weekly)            | 2                | 3                | 4                | 5                | 6                | 8
(Fortnightly
follow-up) | 10               | 12               | 18
(Final visit) |
| Study treatment     |           | X                        | X                | X                | X                | X                | X                |                                 |                  |                  |                     |
| Study day           |           | 0                        | 7                | 14               | 28               | 35               | 42               | 56                              | 70               | 84               | 168                 |
| Window days         |           | +/- 3                    | +/- 3            | +/- 3            | +/- 3            | +/- 3            | +/- 3            | +/- 7                           | +/- 7            | +/- 7            | +/- 7               |

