### **Contact Dermatitis assessment**

As the most likely adverse reaction to study treatment, all participants will be specifically monitored for contact dermatitis at study site throughout each study visit.

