#### Criteria for Postponing or Stopping Study Treatment

##### *Prior to the Application of Treatment*

The treatment should not be applied if, in the opinion of the Investigator, there is a risk that the participant will be unable to tolerate treatment for any reason.

Treatment applications should be deferred if probable ulcer infection is noted. If treatment is deferred the patient can re-enter the trial at the point at which they left once the problem settles and at the Investigator's discretion.

Under these circumstances, at the discretion of the Investigator, study treatment may be postponed and initiated at a later time, provided that:

- The problem that resulted in postponement of the study treatment resolves, and is not considered by the Investigator to be likely to recur; AND
- The relevant visit is still expected to be completed within the stipulated visit window.

Alternatively, the participant may be withdrawn from the study.

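### The primary safety window closes on Day 42, the printed day of the last application, so delayed reactions to that application fall outside the primary analysis

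*Protocol*

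**What the plan says.** Section 2, Table 1 (Study Objectives and Endpoints) gives the primary objective as "To assess the safety and tolerability of PAW up to 6 weeks after initiation of treatment" and ties the analysis to the same period: "The primary safety analysis will be performed based on data collected up to 6 weeks after initiation of treatment". The outcome is how often adverse reactions occur and how severe they are, with irritation and maceration as named examples.

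The schedule of procedures (Section 4, Data collection) marks treatment at six visits ("Study treatment | | X | X | X | X | X | X") and prints their days as "Study day | | 0 | 7 | 14 | 28 | 35 | 42". Overview of Study Visits adds: "A window of plus or minus three days is permitted for Visits 1 to 6". The first follow-up visit, Visit 7, is printed as Day 56 ± 7.

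Section 6, Contact Dermatitis assessment, says: "As the most likely adverse reaction to study treatment, all participants will be specifically monitored for contact dermatitis at study site throughout each study visit".

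Section 7, on treatment before application, says: "If treatment is deferred the patient can re-enter the trial at the point at which they left once the problem settles". The same subsection also makes a postponed start conditional on the visit still fitting its permitted window.

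Two other statements bear on the point. Section 5 (Recording of Adverse Events) has adverse events recorded from consent until completion or withdrawal. Section 9 (Safety Data) tabulates treatment-emergent events by group and states no six-week limit.

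**The concern.** A safety window should extend beyond the last exposure far enough to see what that exposure did. Here the window and the last application end on the same printed day. The reactions the protocol itself expects are local skin reactions, and dermatitis is looked for at study visits. A reaction that develops in the days after Visit 6 would be inspected for the first time at Visit 7, which the primary window never reaches.

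The participants are described in the Risk/Benefit Assessment as mostly neuropathic, so self-report between visits is a weak substitute for inspection.

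What is at stake is the headline result of a first-in-human study with 10 participants per group. For PAW's own reaction rate, events left out can only make the primary figure lower or leave it unchanged. The cut-off is fixed by the protocol's definition of the primary outcome; it is not a detail left to the statistical analysis plan.

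**Working it through.** **Inputs.** Primary cut-off: 6 weeks after first treatment (Table 1). Treatment days as printed: 0, 7, 14, 28, 35, 42, each ± 3 (schedule of procedures). Visit 7: Day 56 ± 7. Participants: 10 per group (Number of Participants).

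**Cut-off day.** 6 × 7 = Day 42. The printed day of Visit 6 is also Day 42.

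**Follow-up inside the window = 42 − day of application.**

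| Visit | Printed day | Days of follow-up to Day 42 | Range with ± 3 days |
|---|---|---|---|
| 1 | 0 | 42 | taken as the start of the window |
| 2 | 7 | 35 | 32 to 38 |
| 3 | 14 | 28 | 25 to 31 |
| 4 | 28 | 14 | 11 to 17 |
| 5 | 35 | 7 | 4 to 10 |
| 6 | 42 | 0 | −3 to 3 |

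A negative value means that the application itself comes after the cut-off, which the visit window allows on Days 43 to 45.

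**Next scheduled inspection.** Visit 7 can fall on Days 49 to 63, which is 49 − 42 = 7 to 63 − 42 = 21 days after the cut-off. It is never inside the primary window.

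**Share of exposure.** One of 6 applications per participant is affected. On PAW that is 10 × 1 = 10 of 10 × 6 = 60 planned applications, or 16.7%.

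**Is the printed day row reliable?** It steps 7, 7, 14, 7, 7, so it jumps from Day 14 (Week 3) to Day 28 (Week 4) although the visits are labelled weekly. It also prints Week 18 as Day 168, whereas 18 × 7 = 126 and 168 / 7 = 24 weeks. Overall Study Design counts 12 visits within the six weeks, but the schedule shows six.

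**Alternative: strictly weekly visits, day = 7 × (week − 1).** The days become 0, 7, 14, 21, 28, 35. Visit 6 is then Day 35, with 42 − 35 = 7 days of follow-up (4 to 10 with the visit window). Visit 7 as printed is still no earlier than Day 49, so no scheduled inspection follows the last application before the cut-off. If Visit 7 (Week 8) is moved by the same rule, it is 7 × 7 = Day 49 ± 7, and only its earliest permitted day, Day 42, touches the cut-off.

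**Deferral.** Under the condition that the visit stays within its window, the latest Visit 6 is Day 45, and a deferred earlier visit stays before Day 42. If the re-entry sentence is read alone and the remaining printed sequence slides, a shift of 1, 2 or 3 weeks puts 1, 2 or 3 applications after Day 42.

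**What one late reaction would do (hypothetical).** For 0/10 the exact 95% upper limit is 1 − 0.025^(1/10) = 30.8%. For 1/10 the exact interval is 0.3% to 44.5%. The protocol plans no such interval; it only shows how much one event matters at this sample size.

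**The case against.** The strongest reply is that nothing is lost to the trial. Adverse events are recorded to the end of participation, with onset dates, and participants are questioned throughout. The Section 9 tables by group carry no six-week limit, so a reaction seen at Visit 7 can still be reported. The analysis is descriptive, with no threshold or decision rule that depends on the window. All of this stands, and it confines the point to what the analysis called primary contains.

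A second reply is that six weeks may mean the Week 6 visit, whenever it takes place. That would bring a Visit 6 on Days 43 to 45 inside the window, but not reactions that appear after it.

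A third is that the Day 42 coincidence rests on an inconsistent row. That is fair. The weekly reading softens the problem to about 7 days of follow-up, but leaves no scheduled inspection before the cut-off.

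Three stronger readings are tempting and are not supported:

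- A reader might infer that the last application has no follow-up at all. Reactions during or just after the ten-minute application on Day 42 are within the window and are watched for at that visit.
- A reader might infer that any deferred application drops out, or that each week of deferral removes one more. The same subsection ties postponement to the visit window, so this follows only if the re-entry sentence is read without that condition.
- A reader might infer that the comparison with saline is biased in PAW's favour. Saline events after the cut-off are left out as well. The downward direction applies to PAW's own rate.

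**Conclusion.** The point holds in a limited form. As printed, the primary safety window ends on the nominal day of the last application. Delayed reactions to that application, and the application itself if given on Days 43 to 45, are outside the primary analysis, although they are recorded and can be reported elsewhere.

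The size is 1 of 6 applications per participant, 10 of 60 on PAW, with 0 days of nominal follow-up (−3 to 3). The other five have 7 to 42 days nominally.

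This assumes that the printed days are right and that six weeks means Day 42. With strictly weekly visits, follow-up is about 7 days (4 to 10), and the absence of a scheduled inspection before the cut-off remains on the printed Visit 7 day. The documents describe no cumulative toxicity and give no rate of delayed reactions, so the number of events that would be left out cannot be estimated.

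**What to change.** In Table 1 and in Section 9, define the primary safety window as running from the first application through the first scheduled follow-up visit after the last application received. For participants on schedule this is Visit 7, Day 56 ± 7. Keep the six-week tabulation as supportive.

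Follow-up after a Day 42 application then becomes 56 − 42 = 14 days nominally, with a range of 49 − 45 = 4 to 63 − 39 = 24 days. A minimum interval of 14 days should not be added. Visits 6 and 7 are nominally exactly 14 days apart, so a slip of one day would move the cut-off to Visit 8 (Day 70 ± 7, up to Day 77) for scheduling reasons alone.

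Two sets of statements must also be reconciled by the sponsor:

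- the study-day row, the weekly label, and the count of 12 visits in six weeks;
- the re-entry sentence and the visit-window condition in Section 7.

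The cost is a few sentences. Visit 7 data are already collected and no treatment rule changes. The downside is small: a somewhat longer window lets in a few more background events, in both groups. The change should be made before unblinding.

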### 3 STUDY PLAN

#### Overall Study Design

This is a randomised, controlled, parallel-treatment study to investigate safety and tolerability of Plasma-activated Water (PAW) in adults with DFU.

Participants will be randomly allocated to one of the two treatment groups:

1. PAW
2. Control (sterile saline)

Participants will receive the appropriate rinse, applied to gauze as a temporary dressing, for ten minutes during a clinic appointment.

**Design:** A randomised, controlled, prospective trial. Participants will be patients with DFU.

**Blinding:** All clinical personnel and all participants will be blind to the assignment and treatment administered (double-blind). Only [name] will retain knowledge of treatment based on preparation of treatment and linkage on a spreadsheet with study ID. This spreadsheet will be used to match for study safety and efficacy on end of study, and/or once an SUSAR has been confirmed.

**Screening and Randomisation:** Participants who provide consent to participate in the study and meet all eligibility criteria and no exclusion criteria will be randomly assigned to one of the two groups.

**Treatment and Evaluation Period:** Participants will attend a total of 12 scheduled visits over 6 weeks, plus follow-up wound review visits fortnightly until week 12 and final visit at week 18.

A study flow diagram is provided in Figure 1.

[figure not shown]

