## **Method of Assigning Participants to Treatment Group**

Participants will be randomly assigned to one of two treatment groups once written informed consent has been obtained and eligibility established.

A participant identification (ID) number will be allocated to each participant who provides informed consent, so that participants can be identified without making assumptions about their subsequent eligibility for the study. Participants will be allocated to sequential, ascending 2-digit ID numbers (e.g, 01, 02, 03), which will provide a unique identifier. The participant will retain the same ID number for the duration of the study.

If a participant fails screening or discontinues from the study, the participant's ID number will not be reused.

Treatments will be prepared according to a list of study IDs and assignments created from random.org, with the spreadsheet of assignment retained by [name]. At no time will [name] have knowledge of patient identity or clinical information for any patient; and at no time will [name] or [name] know the assignment of a patient to PAW or control.

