## **5 ADVERSE EVENTS**

Participants will be questioned and monitored throughout the study with regard to any adverse events (AEs) they may have experienced. An AE can therefore be any unfavourable and unintended sign (including an abnormal laboratory finding), symptom, or disease temporally associated with the use of a medicinal product, regardless of relationship to the medicinal (investigational) product.

Determinations of severity and causality of any AE can only be determined by a clinical Investigator without awareness of whether the treatment used is PAW or control.

An AE shall be classified as serious (a Serious Adverse Event, or SAE) if, in the opinion of either the Investigator or the Sponsor, it:

- Results in death.
- Is life-threatening, i.e., in which the participant was at risk of death at the time of the event.
- Results in permanent impairment of a body structure or body function
- Requires in-patient hospitalisation or prolongation of existing hospitalisation.
- Results in persistent or significant disability/incapacity.

Important medical events that are not immediately life-threatening and that do not result in death or hospitalisation may still be considered serious if, in the opinion of the Investigator, they jeopardise the participant or require intervention to prevent one of the other outcomes listed above. Such events should also be treated as SAEs.

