#### *Follow-Up of Adverse Events and Serious Adverse Events*

All AEs and all SAEs must be followed by the Investigator until resolution, until the AE stabilises or is recognised as a permanent condition by the Investigator, or until the participant is lost to follow-up, whichever comes first. Follow-up investigations may be necessary according to the Investigator's medical judgement.

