## **9 STATISTICAL ANALYSIS**

The statistical analysis principles described below will be supplemented by a statistical analysis plan (SAP), which will be finalised before the database is locked. Any changes to the statistical plans will be described and justified in the clinical study report (CSR).

The SAP will describe procedures for accounting for missing, unused, and spurious data. This section is a summary of the planned statistical analyses of the primary and secondary endpoints.

All analyses, summaries, and listings will be performed using SAS® software (version 9.4 or higher).

The following descriptive statistics will be used as applicable to summarise the study data, unless otherwise specified:

- Continuous variables: sample size [n], mean, standard deviation [SD], median, minimum [min], and maximum [max].
- Categorical variables: frequencies and percentages.

Individual participant data will be presented in listings.

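### As worded, one confirmed SUSAR permits a study-level match of arms to safety and efficacy data, and the end-of-study match is not tied to SAP sign-off or database lock

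*Protocol*

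**What the plan says.** **Who holds the list.** In Section 3, Overall Study Design (Blinding), one role "will retain knowledge of treatment based on preparation of treatment and linkage on a spreadsheet with study ID". Section 3, Method of Assigning Participants to Treatment Group, adds: "Treatments will be prepared according to a list of study IDs and assignments created from random.org".

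**When it is used.** The same Blinding paragraph gives two triggers: "This spreadsheet will be used to match for study safety and efficacy on end of study, and/or once an SUSAR has been confirmed". The Protocol names no other occasion for using the list.

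**What is kept blind.** The Blinding paragraph also says: "All clinical personnel and all participants will be blind to the assignment and treatment administered (double-blind". The section on assigning participants further bars two named roles from ever knowing an assignment. Section 5, Adverse Events, requires severity and causality to be judged by a clinical Investigator "without awareness of whether the treatment used is PAW or control".

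**When the analysis rules close.** Section 9 leaves the handling of missing, unused and spurious data to an SAP "which will be finalised before the database is locked".

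**What the primary outcome rests on.** In Section 2, Table 1: "Assessment of safety will be based on the Incidence and severity of adverse reactions, including but not limited to skin irritation or maceration". The window is six weeks from the start of treatment.

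**The concern.** The sentence on the spreadsheet does two jobs that are better kept apart: the final linkage of arms to outcomes, and the unblinding needed to report one unexpected serious reaction.

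**Scope.** The stated purpose, matching for study safety and efficacy, applies to both triggers. A confirmed SUSAR calls for the assignment of the affected participant. It does not call for a study-level match, and efficacy data add nothing to such a report. A mid-trial match sits badly with the double blind claimed in the same paragraph and with the blinded judgement required in Section 5.

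**Order.** The end of the study is not defined and not linked to database lock. Section 9 sets the SAP's deadline by lock, not by use of the list. The match could therefore come before the rules for excluding data or defining analysis sets are settled.

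At stake is the credibility of a small safety comparison. An adverse reaction is an adverse event judged related to treatment, so the primary outcome depends on a judgement. Choices about data and analysis sets also lose value as evidence if they are made with the arms visible.

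**Working it through.** The Protocol has no figure to reproduce here. Section 9, Sample Size Assumptions, states that no formal calculation was made, and efficacy is to be summarised descriptively. The check is a comparison of passages with a little arithmetic.

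**1. Order of events.** Call the SAP sign-off S, the database lock L and the end-of-study match M. The only ordering that the Protocol fixes is S before L (Section 9). Three sequences satisfy it:

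| Sequence | Match before lock? | Match before SAP is final? |
|---|---|---|
| M, S, L | yes | yes |
| S, M, L | yes | no |
| S, L, M | no | no |

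All three comply with the text, and only the last gives full protection. The Protocol does not say which is intended.

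**2. What could still be open at M.**
- Section 5 says "All AEs and all SAEs must be followed by the Investigator until resolution", or until stabilisation, permanence or loss to follow-up. Some event records may thus be incomplete after the last visit. This concerns the outcome of the event and does not show that causality would be reopened.
- Table 1 takes efficacy data to 18 weeks, while Section 9 (Efficacy Analyses) takes them to 12.
- Section 3 (Replacement of Participants) relies on evaluable participants without defining them.

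The last two are examples of choices that the SAP would have to settle.

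**3. What a SUSAR would reveal.** The planned total is about 20 participants (Section 3, Number of Participants).
- Single-participant code break: 1/20 = 5% of assignments.
- Study-level match on the literal reading, with all 20 enrolled: 20/20 = 100%.

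The second figure depends on reading the SUSAR clause as covering the whole list. The sentence allows that reading but does not compel it.

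**4. Who would be exposed.** Clinical personnel and adverse-event assessors are barred from knowing assignments (Sections 3 and 5). Section 8 says that University investigators and the biostatistician receive de-identified exports; the visible text sets no time at which arms may be joined to them. The exposure therefore lies mainly with those who match, clean and analyse.

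**5. Sensitivity of the primary outcome.** With 10 per arm, moving one participant between having and not having an adverse reaction changes the arm's rate by 1/10 = 10 percentage points. This is the leverage of any single classification in this trial, not an estimate of bias from the wording.

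**6. Chance of a SUSAR.** The Protocol gives no rate. For an assumed per-participant rate p, the chance of at least one in 10 PAW participants is 1 − (1 − p)^10:
- p = 0.01 gives 1 − 0.99^10 = 9.6%.
- p = 0.05 gives 1 − 0.95^10 = 40.1%.

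The answer follows the assumption, so no probability enters the conclusion.

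**The case against.** **The blind is already protected.** This largely stands. The bar on clinical personnel is general, the requirement for blinded causality judgement has no stated end date or SUSAR exception, and two roles are never to know assignments. A reader might infer that after a SUSAR later participants' events would be judged unblinded. That would require breaking these rules, not following them.

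**Only a look-up was meant for a SUSAR.** Possibly. The list stays with one role who already knows every assignment, and the sentence speaks of matching, not of circulating the list. A reader might infer that the whole list, including assignments not yet issued, would be opened. The documents do not say so. What remains is that the words give a study-level purpose, including efficacy, and describe no narrower procedure.

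**Code release belongs in the SAP or an unblinding document.** This carries weight for the end-of-study half, which taken alone is close to missing detail. The Protocol does not say that matching precedes lock, and the unseen SAP may settle the order. But the Protocol itself chose to state the triggers, and an SAP that may be signed after the match cannot be relied on to govern it.

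**The primary outcome is not left open.** Its data end at week 6, follow-up runs to week 18, and causality is to be recorded blind. This weakens any claim that the primary outcome would routinely be undecided at the match.

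**Reporting limits the damage.** All adverse events are documented whatever their cause, treatment-emergent events are tabulated by arm, individual data are listed, and changes to the statistical plans must be justified in the study report. Relabelling an event would not hide it. It would still change the count of adverse reactions, which is the primary outcome.

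**Conclusion.** The point holds in a limited form. The SUSAR trigger is worded as a study-level match that includes efficacy, which is wider than a SUSAR report needs and fits poorly with the Protocol's own blinding rules. The end-of-study trigger permits linkage before the SAP is final or the database locked, but does not plan it.

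The exposure is mainly to data handling and analysis choices; assessors are affected only if the matched file reaches them. Because efficacy is analysed descriptively, the risk is biased classification or selective analysis rather than type I error. The only firm figure is the leverage of one participant in 10, 10 percentage points, and it says nothing about how likely a reclassification is.

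The documents do not support saying that the blind will be broken, that the full list will be disclosed after a SUSAR, or that a SUSAR has any particular probability. Some names are removed from the text, so which roles are kept blind cannot be fully checked. The conclusion rests on the literal wording of one sentence and the absence of a narrower rule elsewhere in the visible Protocol. Label: cheap improvement.

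**What to change.** Replace the sentence on use of the spreadsheet in Section 3 (Blinding) with wording along these lines:

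> For a SUSAR, the list holder will disclose only the affected participant's assignment, to the person responsible for the regulatory report. The list will not then be matched to study safety or efficacy data, and assessing Investigators will remain blind. The full list will be linked to study data only once the SAP is signed, all blinded severity and causality assessments are complete, and the database is locked.

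In Section 9, require the SAP to be final before both database lock and any linkage of assignments, so that the two sections give the same order.

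The change uses the existing list holder and spreadsheet and needs no extra staff, visits or participants. Its one downside is that linkage, and so results, may come slightly later.
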